#### Acceptability of Implant Provision—Client Exit Interviews

During supervisor visits, clients participating in the study will be interviewed by the supervisor in private, before leaving the clinic. They will be asked to rate 7 aspects of service provision on a 5-point scale, with responses being totaled to give a satisfaction score. They will be asked if they would recommend the service to a friend.

Data collection points are summarized in Table 3.

**Table 3 table3:** Summary of data collection procedures.

Timing of data collection	Who collects data, and how	Data to be collected	Sample size
At the time of procedure	Supervisor (if present), observes procedure	Quality of service provision	792
Immediately post implant procedure	Community health extension worker (CHEW), nurse or midwife who conducted procedure, observes client and asks her questions at clinic	Client background, record of procedure including complications at the time	8125
	Supervisor (if present), conducts exit interview with client	Client satisfaction, completeness of counseling information, critical information provision	792
2 weeks post procedure	CHEW, nurse or midwife who conducted procedure, asks client questions at clinic or by telephone	Complications following procedure	4410
Within 30 days of procedure	CHEW, nurse or midwife who conducted procedure, records client’s problems at clinic	Complications following procedure	All cases reported spontaneously at the facility

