## Introduction

In 2012, an estimated 222 million women had an unmet need for modern contraception [1]. Meeting this need would avert an estimated 218 million unintended pregnancies and 118,000 maternal deaths [1]. Nigeria has a large (191 million in 2017) and rapidly increasing population [2] and a high maternal mortality ratio, estimated to be 576 per 100,000 live births in 2013 [3]. In 2013, 15% of currently married women aged between 15 and 49 years were using some method of contraception, a figure considerably lower than the global (63%) and sub-Saharan Africa (27%) estimates for the same year, and 16% had an unmet need for contraception [3].

There are many inequities in contraceptive access, with lower levels of use among women in rural and remote areas, and among those who are poorer, less educated, and younger [4]. In Nigeria, contraceptive prevalence is just 9% in rural areas versus 27% in urban areas [3]. In addition, the most effective contraceptive methods are often the most difficult to access [5]. Long-acting reversible contraceptives (LARCs), such as intrauterine devices (IUD) and implants, are the most effective reversible methods of contraception, with failure rates of between 0.05% and 0.8% in the first year of use (contraceptive pills have a failure rate of 8%) [6]. LARCs also have lower discontinuation rates than short-term methods (such as the pill, injectable, and condom) [5] and generally have high user satisfaction [7]. In sub-Saharan Africa, unlike Asia and North America, short-term contraceptive methods dominate [8]. In Nigeria in 2013, 9.8% of currently married women were using a modern method of contraception, and most (7.1%) were using short-term methods; just 1.1% were using an IUD and 0.4% an implant [3].Contraceptive implants consist of flexible matchstick-sized rods, inserted below the skin on the nondominant upper arm. They release small amounts of progestin hormone to prevent pregnancy for 3 to 5 years [9]. Insertion is quick and does not require pelvic examinations or laboratory tests. Complications are rare (although may include infection at the insertion site, expulsion, or difficult removal), and once inserted, implants require no regular action by the user or health system [6].

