### Site and Provider Selection

The study will take place in public sector facilities in 2 Nigerian states, 1 in the north (Kaduna) and 1 in the south (Ondo). The north and south of Nigeria differ in religious beliefs, contraceptive prevalence rate, and availability of health care providers, making it necessary to generate evidence in each context. We will purposively select local government areas (LGAs) in Kaduna and Ondo States for study participation by excluding LGAs with overlapping interventions and, given the extensive supervision needs of the study, hard-to-reach LGAs.

Facilities will be eligible if they provide referral services on site or are located within 20 km of a referral facility, in case of adverse events resulting in the need to refer clients; if there is a provider interested in participating in the study who expects to be in the facility for the 12-month period of client recruitment; and if the facility has been providing FP in the previous 3 years and does not currently provide implants. Larger urban centers staffed by nurses, midwives, and CHEWs and smaller rural health centers staffed by a nurse or midwife only will be eligible for inclusion.

A total of 60 facilities will be selected in each state from eligible facilities, yielding a total of 120 facilities. Where there are more than the required number of eligible facilities, simple random sampling will be used to select facilities for inclusion. At least 30 nurse or midwife-led facilities will be selected in each state to allow inclusion of 30 nurses and midwives in the study. The remaining 30 facilities will include as many CHEW-led facilities as possible. From each CHEW-led facility, 1 CHEW will be trained, and 1 nurse or midwife or 1 CHEW will be trained from each nurse or midwife-led facility. The providers trained will be the individuals responsible for providing FP services at their facility.

**Table 1 table1:** Details of implant brands to be included in the study.

Product	Composition	Labeled duration of use	Format
Jadelle	150 mg levonorgestrel, 2 rods	5 years	2 rods, separate disposable trocar
Implanon Classic	68 mg etonorgestrel, 1 rod	3 years	1 rod preloaded in trocar

**Table 2 table2:** Implant insertion adverse events to be recorded.

Description of adverse reaction		Day recorded relative to procedure
Anaphylactic reaction to the implant		0
Implant insertion unsuccessful on first or second attempt		0
Implant breaks		0

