Palpitations resulting from the local anesthetic		0
Expulsion of implant		14
Paresthesia due to neural damage (numbness, tingling, tickling, pricking, or burning sensation at implant site)		14
Pain post procedure for >1 week and requires further outpatient observation and medical intervention		14
**Infection**		0
	Local redness swelling	14
	Discharge	14
	Fever	14
Scarring		14
Hematoma or bruising requiring medical intervention		0 and 14
Bleeding around the injection area		0 and 14
Other adverse reaction requiring medical treatment or resulting in long-term incapacity or fatality		0 and 14

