### Participant Recruitment and Eligibility

Women requesting an implant from a participating facility will be eligible to participate if they are aged between 18 and 49 years and are eligible to have the implant. On presenting at a participating clinic, each client will be provided with comprehensive FP counseling and offered all available FP methods (balanced counseling technique) [25]. Participating providers will invite all clients who request an implant, and meet the inclusion criteria, to participate in the study, using a study information sheet and consent form. If the client chooses an implant, she will be offered Jadelle or Implanon Classic, and the same service provider will do the insertion. Clients who want an implant but do not want to participate in the study will be advised of the nearest available facility providing this service.

Clients will be recruited until the sample size is reached (anticipated to be approximately 7 months). Participants who are asked to return for a 2-week follow-up visit will be reimbursed for their travel costs. Women who do not return after 14 days will be contacted by telephone (if they gave consent to be contacted and a phone number). In total, 3 attempts will be made to contact women by telephone before they are considered lost to follow-up. Those who are contacted by phone will be asked to attend the facility for the 14-day follow-up visit or, if unable, to answer questions over the telephone.

The number of clients who refuse to take part and who withdraw will be documented, along with the reason for refusal or withdrawal where given. If they agree, very basic sociodemographic data and the reason for refusal will be recorded.

All health care staff at participating facilities will be eligible for participation in semistructured in-depth interviews to assess acceptability of CHEW implant provision. A range of staff types (doctors, nurses, midwives, and CHEWs) will be approached by a senior research staff member and asked for their willingness to participate. Policy makers involved in FP will be contacted individually by researchers and asked to participate in an interview. All participants will be asked for their informed consent before the interview.

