### Data Collection

#### Safety—Days 0 and 14

At the time of insertion, the provider will record baseline data about the implant insertion, the occurrence of adverse events, and the client’s background (including demographics, socioeconomic information, reproductive history, and reasons for getting an implant). At day 14 post insertion, the provider will ask the client about side effects or complications arising from the procedure.

To assess the ongoing safety of the study, any participant coming to the facility with complaints about her implant up to 30 days after the procedure will be asked a few questions by the provider about what the participant has experienced and her responses will be documented. Responses will be reviewed by project staff.

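### Day-14 safety events that can be seen or felt are ascertained only by asking the woman, so missed events can pull the comparison towards noninferiority

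*Protocol article*

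**What the plan says.** The primary objective (Study Design, Aim, and Objectives) compares safety on the day of insertion and up to 14 days afterwards.

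- **Day-14 method.** Data Collection, under Safety—Days 0 and 14, states: "At day 14 post insertion, the provider will ask the client about side effects or complications arising from the procedure". The column of Table 3 on who collects data and how gives the same method for the 2-week contact: "CHEW, nurse or midwife who conducted procedure, asks client questions at clinic or by telephone".
- **Day-0 method.** The same column says that immediately after the procedure the provider "observes client and asks her questions at clinic".
- **Telephone.** Under Participant Recruitment and Eligibility, women who do not return and who agreed to be phoned are "asked to attend the facility for the 14-day follow-up visit or, if unable, to answer questions over the telephone".
- **Day-14 events.** Table 2 assigns to day 14 "Expulsion of implant", local redness or swelling, discharge, fever, scarring, paresthesia, prolonged pain, and (at both time points) bleeding and hematoma or bruising that needs medical intervention.
- **Bias check.** The Discussion concedes that providers assess their own practice and plans to compare event rates recorded by supervisors with those recorded by providers. The supervisor tasks described in Data Collection and Table 3 are observation of insertions and exit interviews on the same day.
- **Analysis.** Data Analysis plans a complete case analysis and a risk difference with 95% CI. It does not mention contact mode.

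**The concern.** The method does not fit the outcome. Redness or swelling, discharge, expulsion and scarring are found most reliably by looking at and feeling the arm. The plan's own list of reportable moderate events includes partial expulsion, which a woman may not notice. Table 3 uses a stronger method at day 0 and a weaker one at day 14 in the same column, so this is a stated choice and not a detail lost in condensing the protocol.

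In a superiority trial, missed events would mainly cost power. Here they work in favour of the conclusion the study hopes to reach: if each arm loses the same fraction of its events, the absolute difference shrinks by that fraction while the margin stays put. What is at stake is the day-14 half of the primary safety claim.

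**Working it through.** **1. The plan's own figure.** Sample Size, By Day 14, gives a limit of 1%, 80% power and 1225 per arm, but no event rate. With the same rate p in both arms, n = (z₁₋α + z₀.₈)² × 2p(1−p) / margin². Setting p = 1% and one-sided α = 5%:

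(1.645 + 0.842)² × 2 × 0.01 × 0.99 / 0.01² = 6.183 × 198 ≈ 1224.2, rounded up to 1225.

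The figure is reproduced, and p = 1% is therefore a back-solved value. Then 2450 × 1.5 = 3675 and 3675 × 1.2 = 4410, as stated. The 1225 is the number per arm before the design effect, so it serves as the effective size below.

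**2. Equal under-detection.** Assumptions not in the documents: true rate 1% for nurses and midwives; the CHEW rate higher by exactly the margin; a fraction S of events detected in both arms; no false positives. The test uses the upper limit of a two-sided 95% CI, as in Data Analysis (nominal one-sided error 2.5%).

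- Observed difference: D = S × (p_CHEW − p_nurse)
- SE = √{[S·p_nurse(1−S·p_nurse) + S·p_CHEW(1−S·p_CHEW)] / 1225}
- Probability of declaring noninferiority: Φ((margin − D)/SE − 1.96)

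For S = 0.8 and a 1% margin, observed rates are 0.8% and 1.6% and D = 0.8 points. SE = √[(0.007936 + 0.015744)/1225] = 0.00440. Then (0.010 − 0.008)/0.00440 − 1.96 = −1.505, and Φ = 6.6%.

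For S = 0.5 and a 1% margin, observed rates are 0.5% and 1.0% and D = 0.5 points. SE = 0.00348. Then 1.435 − 1.96 = −0.525, and Φ = 30.0%.

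| Margin | True rates (CHEW / nurse) | S = 1 | S = 0.8 | S = 0.5 |
|---|---|---|---|---|
| 1% (Sample Size) | 2% / 1% | 2.5% | 6.6% | 30.0% |
| 2% (Abstract, Data Analysis) | 3% / 1% | 2.5% | 12.1% | 70.2% |

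Both margins are shown because the article uses both.

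**3. Differential under-detection through the telephone.** Further assumptions: in-person questioning finds every event and a telephone call finds half. Then S = 1 − telephone share × 0.5.

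- Telephone share 30% for CHEW clients and 10% for nurse clients: observed rates 2 × 0.85 = 1.70% and 1 × 0.95 = 0.95%, D = 0.75 points. False noninferiority at the 1% margin is 7.8%.
- Shares reversed: 2 × 0.95 = 1.90% and 1 × 0.85 = 0.85%, D = 1.05 points, so the bias runs against CHEWs.
- Shares equal at 30%: D = 0.85 points, false noninferiority 5.2%.

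The sign of any differential part depends on which cadre's clients are phoned more often. The equal part always shrinks the difference.

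**The case against.** Much of the case against has force.

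- **Several items suit a question.** Paresthesia, fever and prolonged pain are symptoms. Hematoma counts only if it needed medical intervention, which a woman can report, and discharge and bleeding can often be reported too. Complaints brought to the facility within 30 days are also recorded. This limits how far detection falls. It does not cover signs the woman does not notice or does not mention.
- **Telephone is a fallback.** All women are asked to return until 4410 is reached, and those phoned are first asked to attend. This stands: a telephone answer is better than a loss. Asking without looking applies in clinic as well.
- **Every detection rate above is assumed.** This stands. The working shows direction and sensitivity, not an estimate. Under the 2% margin, a true excess of between 1 and 2 points would be acceptable, which is why the second row of the table takes a true excess of 2 points.
- **Inspection would be by the same unblinded provider.** This is true, and the article admits self-assessment as a limitation. A defined look-and-feel step still leaves less to recall.

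A reader might infer three stronger points, none of which the documents support.

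- *Rod placement is never checked.* Table 2 has a day-0 event, "Implant insertion unsuccessful on first or second attempt". Correct insertion is part of the quality definition and of supervisor observation (792 insertions planned). Providers need 5 successful supervised insertions of each brand before accreditation.
- *The bias favours CHEWs as the more remote cadre.* The Discussion mentions remoteness only as a possibility, and in relation to supplies. Rural centers staffed only by a nurse or midwife are eligible, and hard-to-reach LGAs are excluded.
- *The plan misses difficult removal.* The Introduction lists it among rare complications, but nothing in the article ties it to a fault detectable by day 14, and removal comparisons are openly placed out of reach.

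**Conclusion.** The concern holds in a limited form. The stated day-14 method is questioning alone, by the provider under evaluation, for an outcome that includes several visible or palpable signs. No site inspection and no supervisor check at day 14 is described. Under-detection, even if equal by cadre, moves the risk difference towards zero and makes noninferiority easier to conclude.

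The size cannot be fixed from the documents. The figures of 6.6% and 30%, against a nominal 2.5%, rest on the assumed 2% versus 1% rates, 1225 effective per arm, the 1% margin, and detection of 80% or 50%. Unequal telephone use could add to or offset this, and the article does not show which.

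**What to change.** In Data Collection (Safety—Days 0 and 14) and in the 2-week row of Table 3, have the provider inspect and feel the insertion site at every in-person day-14 visit and record the Table 2 signs, with questions kept for symptoms and for women reached only by telephone. Record contact mode, report its share by cadre, and repeat the day-14 comparison in women seen in clinic as a sensitivity analysis.

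Costs: a short step at a visit already held, one form item for contact mode and one extra analysis. The clinic-only analysis is less precise, and women who return may differ from those who do not, so it supports the main analysis without replacing it. Better detection may also raise the event rate. By the formula in step 1 of the working, a rate of 1.5% instead of 1% would need 6.183 × 2 × 0.015 × 0.985 / 0.01² ≈ 1827 per arm before the design effect.

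The Results section says recruitment ended in December 2016, so the form change is a lesson for design. For this study, the report can still state whether the site was examined at day 14. It can also give contact mode by cadre and the clinic-only comparison if mode was recorded, or name its absence as a limitation.

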#### Acceptability of Community Health Extension Worker Implant Provision to Health Care Staff and Policy Makers

Interviews with staff members and policy makers will cover themes such as perception of confidence and competence in CHEW provision of insertions, support for policy change, perceptions of effectiveness of demand-generation activities, supervision levels, supply chain, and cost-effectiveness. Responses will be recorded on paper using shorthand notes with verbatim quotes as far as possible, and audio-recorded as a backup.

### Data Management

Client identifiers, such as name or phone number, will be recorded in a client register and will not be included on client data collection forms. The 2 forms will be stored separately and linked using a client identification number. Study documents will remain in locked cabinets in the provider’s office, if available, or in a secure location where medical records are secured.

Providers will keep the anonymized data collection forms for 30 days after insertion and will record any spontaneous client reports of adverse events over this 30-day period. After 30 days, the anonymized forms will be sent to MSION head office in Abuja. The client register will be kept at the clinic for the duration of the study. At the end of the study, client registers will be sent to MSION head office in Abuja and will be kept in a locked cabinet separate from data collection forms. Completed and anonymized exit surveys will be kept on the person of the clinical supervisor or researcher conducting the interview until the end of the visit, after which they will be sent to MSION in Abuja.

Data entry will be conducted by an independent consultant engaged by MSION. Paper forms will be checked for completeness and obvious errors by the data entry clerk when they arrive in Abuja, and queries will be checked by telephone with the provider, clinical supervisor, or researcher. The data entry clerk will double-enter all data into a password-protected electronic database, verify any discrepancies between the 2 data entries, and clean the data in preparation for safety monitoring analysis every 3 months. When all complication data have been collected, entered, and cleaned, the full dataset will be transmitted to the research team in MSI London for analysis.

The cleaned, anonymized electronic dataset will be kept by MSI London for a minimum of 5 years and will be made publicly available by request to Marie Stopes [27]. Paper forms will be kept securely by MSION in Abuja until 1 year after publication and then destroyed.

Audio recordings will be transcribed verbatim. The recordings will be stored in locked cabinets until they have been transferred to a computer, after which they will be destroyed.

### Data Analysis

Quantitative data will be analyzed using statistical software Stata, version 13 (Stata Corp. College Station, Texas). Complete case analysis will be conducted. For safety monitoring, complication rates by provider will be generated by the study manager in Abuja every 3 months, to identify any providers with unusually high complication rates. These data will be checked and response activities will be agreed at the 3 monthly technical advisory committee meetings to be held in Abuja, which will be attended by staff from MSION and MSI, and ministry of health officials.

Training and supervision data will be presented using descriptive statistics. Insertion adverse events of CHEWs will be compared for noninferiority against the complication rates of nurses and midwives. To assess the equivalence between the nurses and midwives and the CHEWs, the risk difference between the 2 provider types together with their 95% CI will be derived by use of a generalized estimating equation model to adjust for clustering. If the CI of the risk difference between the 2 groups falls within the predetermined margin of equivalence (–2% to 2%, which is equivalent of lower bound of one side 97.5% CI), the 2 types of service providers can be considered equivalent.

Sensitivity analysis will be designed to control for group assignment bias among the 2 states. They will be analyzed both separately and together to identify any differences in performance between CHEWs in the northern state compared with the southern state.

All quality and acceptability indicators will be weighted equally, except for those most critical (infection prevention, correct clinical technique, and advice on where to go in case of problems), which will be given a higher weight. The difference in mean quality and acceptability scores between CHEWs and midwives will be compared using a *t* test.

Analysis of qualitative data will be undertaken manually or using a qualitative analysis software such as N-Vivo. Quotations will be labeled by cadre of speaker, and a thematic analysis will be carried out. Transcripts will be read and reread. Extracts will be coded according to themes and subthemes that emerge from the data or that have been identified before the analysis such as those included in the in-depth interview guide. A selection of quotes representing different cadres and views will be used to write a report structured around these themes.

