### Sample Size

#### Day of Insertion

Calculation of the number of participants required for the study is based on the primary outcome—the frequency of adverse events associated with insertion on the day of the procedure.

Studies documenting adverse events of implant insertion on the day of procedure have found them to be rare. For example, a randomized clinical trial of 2008 women found that 0.2% clients using Jadelle and 0.8% clients using Implanon Classic experienced complications at insertion [26].

To detect a difference in proportion of adverse events between the 2 study arms with a noninferiority limit of 0.5%, 80% power, and 95% confidence level on the day of implant insertion, we would require a sample size of 2462 in each study arm, giving a total sample size of 4924. To account for possible clustering, we will include a design effect of 1.5, increasing the sample size to 7386. To allow for incomplete records, we will increase this by 10% to a total sample size of 8125.

We estimate that each provider will receive approximately 10 insertion clients per month and that we may see a refusal rate of 20%. With a total of 120 providers, we expect to recruit 1200 clients per month. We would therefore need to recruit clients for approximately 7 months to achieve the required sample size for insertions.

#### By Day 14

We expect the number of adverse events observed by day 14 to be higher than that at day 0 as we may start to see infections. This reduces the required sample size needed to detect a difference between health care provider types. To detect a difference in proportion of adverse events between the 2 study arms with a noninferiority limit of 1%, 80% power, and 95% confidence level 14 days after implant insertion, we would require a sample size of 1225 in each study arm, giving a total sample size of 2450. To account for possible clustering, we will include a design effect of 1.5, making the size 3675. Assuming 20% loss to follow-up makes a total sample size of 4410. If we expect to recruit 1200 clients per month, it will take around 4 months to recruit the sample size we require.

All recruited clients will be asked to return to the inserting provider for a follow-up visit at 14 days post insertion until the sample size of 4410 is reached.

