## Discussion

Besides resulting in 120 more health care staff qualified to provide contraceptive implants, this study will provide robust evidence on the safety, quality, and acceptability of contraceptive implant provision by CHEWs compared with nurses and midwives in Nigeria. This evidence may also serve to support future decision making about task-sharing implant services to community health workers in other countries. Strengths of the study include being able to compare CHEW provision with an existing standard of care (nurse and midwife provision). The study builds on existing training and supervision procedures, which will increase the sustainability and scalability of CHEW implant provision if the results are promising.

The main limitations of the study are the lack of randomization and that that providers will be assessing their own practices. Clients cannot be randomized because they usually access their local area clinic, and providers cannot be randomized because they work at either CHEW-led or at nurse- or midwife-led public clinics. Where both cadres work together, the national policy is to train 1 provider in each clinic. This could result in bias due to nonequivalence of the intervention and control groups (ie, if participating CHEWs tend to work in more remote clinics with poorer supply chain for infection prevention supplies than participating nurse and midwives). It is not feasible to arrange independent observation of all procedures; furthermore, observation itself may change practice. Bias will be assessed by comparing adverse event rates recorded by supervisors with those documented by providers themselves. Providers will be informed that this checking will take place.

Although both CHEWs and the nurses and midwives will be trained in and will conduct implant removals, there will be insufficient time during the study period to collect enough information on removals to make any noninferiority comparisons.

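### The nonrandomized cadre comparison is adjusted for clustering only, and analysing the two states separately and together cannot control group assignment bias as the article says it will

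*Protocol article*

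**What the plan says.** The Data Analysis section fixes the safety comparison as a risk difference with a 95% CI that "will be derived by use of a generalized estimating equation model to adjust for clustering". No covariate, matching, weighting or stratification is named for it.

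The same section then states: "Sensitivity analysis will be designed to control for group assignment bias among the 2 states". The next sentence gives the content: "They will be analyzed both separately and together to identify any differences in performance between CHEWs in the northern state" and those in the southern state.

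The Discussion lists the lack of randomization as a main limitation and says of it: "This could result in bias due to nonequivalence of the intervention and control groups". Its example is CHEWs working in remoter clinics with poorer infection-prevention supplies. The one other bias check described there compares supervisor-recorded with provider-recorded event rates.

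Brand is left to the client: "If the client chooses an implant, she will be offered Jadelle or Implanon Classic". The Day of Insertion section cites a trial in which "0.2% clients using Jadelle and 0.8% clients using Implanon Classic experienced complications at insertion". On data, Data Collection says "the provider will record baseline data about the implant insertion, the occurrence of adverse events, and the client’s background", the last covering demographics, socioeconomic information and reproductive history.

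Results reports 30 CHEWs and 30 nurses/midwives trained in each state.

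**The concern.** A GEE that accounts for clustering gives a valid standard error for the contrast. It does not make the two groups comparable. In a quasi-experimental design the comparability has to come from somewhere else, and the only analysis the article offers for it is the state split.

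That split answers a different question, namely whether CHEW performance differs between north and south. The two cadres have equal provider numbers in each state, so state is at most a weak confounder. The differences that could bias the contrast lie within a state: which clinics the cadres work in, which clients attend and which brand is inserted. Splitting by state leaves all of these in both halves.

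At stake is a noninferiority conclusion that partly reflects case mix. Adverse events are rare and the margins are stated in absolute percentage points, so a small absolute imbalance matters more the tighter the margin.

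**Working it through.** **1. Does the state split control cadre assignment?** Confounding by state requires cadre share to differ by state. Among providers it is 30/60 = 50% CHEWs in each state. State can confound only through unequal client volume per provider, which the article merely estimates (about 10 insertion clients per provider per month). Site and Provider Selection ties cadre to facility type inside each state: CHEW-led facilities supply only CHEWs. A separate analysis within each state inherits that link.

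**2. Reproducing the plan's day-0 sample size**, to fix a baseline rate and an effective sample size. The event rate is not stated. I assume p = 0.5%, the midpoint of the cited 0.2% and 0.8%, and one-sided 5%:

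n per arm = (1.645 + 0.842)² × 2p(1 − p) / δ² = 6.18 × 0.00995 / 0.005² ≈ 2461, against 2462 stated. Then 2462 × 2 × 1.5 = 7386, and × 1.1 = 8124.6, rounded to 8125. I use 2462 per arm as the effective size after the design effect.

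**3. Size of an unadjusted imbalance, using brand.** The rate ratio is 0.8/0.2 = 4 and the absolute difference is 0.6 points. With no true cadre effect:

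spurious risk difference (CHEW minus nurse/midwife) = (difference in Implanon Classic share) × 0.6 points.

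The article gives no brand mix by cadre, so the shares are assumptions.

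| Assumed Implanon share, one cadre v the other | Shift | Of 2% decision margin | Of 0.5% sample-size margin |
|---|---|---|---|
| 60% v 40% | 0.2 × 0.6 = 0.12 points | 6% | 24% |
| 70% v 30% | 0.4 × 0.6 = 0.24 points | 12% | 48% |
| 100% v 0% (extreme) | 0.60 points | 30% | 120% |

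**4. Effect on the conclusion** (normal approximation, 2462 effective per arm).

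- Stated decision rule, 2% margin, no true cadre effect: SE = √(2 × 0.005 × 0.995 / 2462) = 0.20 points, so the 95% half-width is about 0.39 points. A 0.24-point shift against CHEWs puts the worse limit near 0.24 + 0.39 = 0.63 points, well inside 2. Noninferiority is still concluded.
- Same margin, CHEWs truly worse by exactly 2 points but inserting more Jadelle: false noninferiority rises from 2.5% to about 5% with a 20-point share difference and about 10% with 40 points. The formula is Φ(shift/SE − 1.96). For 20 points the SE is 0.345 points, giving Φ(0.12/0.345 − 1.96) = 5.3%. For 40 points it is 0.346, giving Φ(0.24/0.346 − 1.96) = 10.3%.
- 0.5% margin, one-sided 5%: with no true effect and more Implanon among CHEWs, the 80% chance of concluding noninferiority falls to about 60% at 20 points. With CHEWs truly worse by 0.5 points and inserting more Jadelle, false noninferiority rises from 5% to about 12%.

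**5. Events available for adjustment** at the assumed 0.5%: 8125 × 0.005 = 40.6. After 10% incomplete records, 8125 × 0.9 × 0.005 = 36.6. So about 37 to 41.

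**The case against.** Five points can fairly be made on the other side.

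- **Margin.** The decision margin is 2% (Abstract and Data Analysis), and 0.5% appears only in the sample-size calculation. A reader might infer that modest brand imbalance would decide the study. Under the stated 2% rule it would not hide noninferiority, and it could produce it falsely only when the true excess is already near 2 points. This stands. The disagreement between the two margins is a separate issue.
- **Brand.** Both cadres are trained, accredited and offering both brands, and no imbalance is documented. The cited rates concern complications at insertion in one trial, whereas Table 2 is broader. If counseling influences the choice, brand is partly a consequence of the provider. All of this stands, so brand is an illustration and not a predicted bias.
- **Silence.** A full protocol or SAP, not shown, may list covariates. A reader might infer that no adjusted analysis was ever planned, and the article does not establish that. The objection does not reach the state split, which the article itself describes as control of assignment bias.
- **Direction.** The Discussion's example would count against CHEWs and so is conservative for noninferiority. That holds for that example. Brand or client mix could act either way.
- **Remedy.** A reader might infer that a facility-type term solves the problem with data in hand. CHEW-led sites contain no nurses or midwives, so the term may be nearly or fully collinear with cadre. Nor are clinic remoteness and supplies among the data the article says are collected.

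**Conclusion.** The point holds in a limited form. The article states a crude, clustering-adjusted risk difference for a nonrandomized comparison, and it describes as control of group assignment bias an analysis that cannot provide it. That follows from the text and from the 30/30 provider split in each state, without any assumption about event rates.

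The size is moderate. Under assumed 20- and 40-point brand imbalances the shift is 0.12 and 0.24 points: small against the 2% decision margin (6% and 12%), and material against the 0.5% sample-size margin (24% and 48%). Brand alone cannot move the risk difference by more than 0.6 points at the cited rates. These figures rest on the cited rates carrying over to this study, on an assumed brand mix, and on an effective 2462 per arm. The bias from clinic setting, which is the one the Discussion names, cannot be sized from the document.

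**What to change.** 1. Keep the crude GEE and report beside it an adjusted risk difference with provider-level clustering. Standardize it from a regression model or obtain it by propensity weighting, using state and a short list drawn from the client background already collected.
2. Show the adjusted estimate with and without implant brand, because counseling may influence brand.
3. Describe the state analysis as heterogeneity by state, tested with a cadre-by-state interaction, and drop the statement that it controls group assignment bias.
4. Leave facility type out of the primary model. If enough CHEWs work in nurse/midwife-led facilities, add a comparison restricted to those facilities as a sensitivity analysis, and report how many CHEWs it rests on.
5. State that remoteness and supply differences may remain unmeasured.

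The cost is analysis wording and code, with no new data for items 1 to 3. The downsides are real. About 37 to 41 expected day-0 events (at an assumed 0.5% rate) allow only a few covariates. The adjusted estimate cannot remove confounding by setting that was not recorded. Results says data cleaning was complete and analysis was being finalized, so the adjusted estimate should be labelled as added late.
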